### Adverse event reporting and harms

Medical history records will be prepared for each patient, which will include the results of the standard laboratory examinations before the start of the study and after 8 weeks of treatment. Standard laboratory examinations will include the following: routine blood tests, routine urine tests and indices of renal function (uric acid, creatinine and urea) and hepatic function (alanine aminotransferase, aspartate aminotransferase, total bilirubin and γ-glutamyl-transpeptidase).

At each of the 2-week visits during treatment, the investigator will collect data pertaining to all adverse events (AEs), their severity, and their potential relationship to treatment. The safety assessment will include the determination of the incidences of treatment-related adverse events (trAEs) or SAEs, the rate of trAEs contributing to discontinuation, and changes in laboratory parameters. If SAEs occur, all medications and therapies in this trial will be discontinued immediately.

Any treatment and results of AEs during the study should be recorded in the AE list. Researchers should decide the diagnosis, treatment measures, and follow-up forms according to the severity of AEs, such as hospitalization, outpatient service, home visit, telephone, and so forth, until the laboratory index returns to normal and the symptoms and signs disappear. The cost of handling all trAEs should be borne by the unit responsible. In case of SAEs, the subcenter will take immediate measures necessary to protect the safety of the patients.

## Discussion

Psoriasis is an immune-related disease characterized by a gradual long-term development and frequent recurrence of symptoms; it has been shown to negatively affect the quality of the life in adults and children due to social isolation, occupational stress and stigmatization [29–36]. On the basis of an in-depth survey of the recent clinical trials and research on the underlying mechanisms, we found that psoriasis is a chronic multisystem inflammatory disease associated with a variety of related complications, including hypertension, cardiovascular disease, metabolic syndrome, malignant tumors and inflammatory bowel disease [37, 38]. Moreover, psoriasis has emerged as a condition that is indicative of an increased risk of disease and death associated with these complications [39].

Three types of psoriasis syndrome are widely recognized based on TCM theory, namely blood heat, blood stasis and blood dryness. Blood heat is considered a key pathological factor in the progression of psoriasis, while blood dryness is mostly caused by long-term psoriasis symptoms. Blood stasis may be present throughout the course of the disease, especially in plaque psoriasis. TCM is widely applied as the first-line treatment for mild-to-moderate psoriasis due to its suitability for long-term use at reasonable compatibility and doses [40]. JY is a representative prescription for the blood-heat syndrome of psoriasis and in the treatment of plaque psoriasis. It consists of seven constituents that are involved in clearing of heat, cooling of blood, and detoxifying and removal of blood stasis.

In a previous study, we have found that JY prescription was an effective and safe medication for mild-to-moderate psoriasis vulgaris, with no obvious adverse reactions [12]. In addition to mechanistic research, we have also conducted acute and chronic toxicity tests for 6 months in a mouse model of psoriasis and found that treatment with JYG did not result in any significant abnormalities in the physiological parameters or pathological changes in the major organs of rats [41]. We therefore considered JYG as a safe and effective medication for the treatment of psoriasis. Results from a pooled analysis conducted by us also indicated that levels of interferon-γ, IL-17, IL-23, and tumor necrosis factor-α were significantly increased, whereas those of IL-4 and IL-10 were significantly decreased in the sera of patients with blood-heat syndrome of psoriasis [42]. Determining the effect of the JY prescription on the aforementioned immune factors will be a focus area of our future research. To ensure the high treatment compliance in the present trial, we intend to use JY prescription granules instead of Chinese herbal medicine, owing to the establishment of its quality control standard using high-performance liquid chromatography [43].

Many clinical trials in China have shown that the combination of oral TCM and external treatment for psoriasis show superior clinical effects compared to individual TCM treatment or external treatment. The moving cupping therapy is particularly effective for the treatment of plaque psoriasis because it is noninvasive with no side effects and is therapeutically advantageous, simple, convenient and inexpensive. Furthermore, it promotes lesion thinning and regression. Considering that the efficacy of moving cupping therapy in the 8-week treatment of plaque psoriasis was higher than that in the 4-week treatment [44], we designed the entire treatment cycle to run for 8 weeks.

In the present study, patients with mild-to-moderate psoriasis will be treated with TCM. After 4 weeks of treatment, depending on whether PASI 75 is reached, the necessity to adjust treatment from JYGP to JYG or the moving cupping placebo therapy to moving cupping therapy will be evaluated. This novel study design facilitates not only a comparison of the curative effects of internal and external TCM treatments, but also enables an assessment of the intervention opportunities for internal and external treatment with TCM. The use of sequential treatment of TCM is in line with clinical practice.

For the purpose of the present trial, we intend to conduct NB-UVB phototherapy three times weekly because additional exposure and higher UVB doses can increase the incidence of adverse reactions, although for some patients a frequency of five exposures a week is associated with a more rapid cure of psoriasis [45, 46]. Moreover, NB-UVB phototherapy three times a week can be combined with moving cupping therapy to enhance patient compliance. Patients with severe plaque psoriasis will be treated separately with TCM, WM or TCM + WM to achieve rapid and long-term effects with no side effects and to establish high-level clinical evidence and treatment norms for integrated Chinese and western medicine.

In addition, the use of a moisturizer is necessary in any course of treatment for plaque psoriasis. Therefore, all the patients in this study will receive a basic skin care product (YuZe Skin Barrier Recovery Body Lotion®, a moisturizer containing linoleic acid-ceramide). Clinical trials have shown that local use of this moisturizer can relieve psoriasis and may be an effective approach in its treatment and prevention [47].

According to the 2018 guidelines for the diagnosis and treatment of psoriasis, TCM is the first choice of treatment for mild-to-moderate psoriasis, while integrated traditional Chinese and western medicine is needed for the treatment of severe psoriasis [26]. In this trial, we will compare TCM granules, moving cupping therapy, and NB-UVB phototherapy with placebo granules or placebo therapy to obtain a high-grade clinical evidence for the clinical application of this guideline. There is no stratification based on TCM syndromes because JYG can clear heat, cool blood and detoxify and remove blood stasis. A large cohort study on the syndrome differentiation and treatment of TCM for psoriasis vulgaris has been carried out in another subtopic of the National Key Research and Development Program of China [48]. As an important part of the research project, this study will contribute to determining the basic principles and application of the “new blood syndrome theory” and promote the innovation of the academic connotation of “TCM differentiation of blood treatment theory” for psoriasis. The results will provide a new perspective on the timing and options for therapy, based on internal and external TCM treatments and integrated Chinese and western medicine treatments for plaque psoriasis.

Our study has a few limitations, explained as follows. First, although all results will be measured and recorded by independent researchers to minimize the risk of detection bias, we cannot use a double-blind procedure in the moving cupping therapy and NB-UVB phototherapy. Second, small deviations in the manipulation of operators implementing moving cupping therapy are inevitable, but performance bias can be reduced through unified professional training. At present, a research team is developing negative pressure-controllable moving cupping appliances, which are expected to be used in future clinical trials.

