### Trial design

This is a multicenter, single-blinded, randomized controlled trial that aims to determine the appropriate time for the intervention with TCM and involves a sequential treatment plan for severe psoriasis by combining TCM and WM.

The study consists of three phases: screening, treatment and follow-up. During the initial screening period, patients will be recruited to dermatological clinics for body surface area (BSA) assessments and laboratory tests (including pregnancy tests for women of child-bearing age), and they will also be assessed on the designated inclusion and exclusion criteria. The eligible patients will be required to sign a written informed consent form, including an option to participate in the biobank initiative. The investigator will clearly explain to the patients all the details in the consent form, ensuring that they are fully aware of their rights and are able to cooperate with the researchers to complete both the treatment and follow-up phases. Patients who provide their informed consent and meet the laboratory test criteria will undergo the medical procedures, based on their BSA score. According to the latest Chinese guidelines for severity, psoriasis is classified into the following categories: mild (lesion area <3% BSA), moderate (lesion area 3–10% BSA) and severe (lesion area >10% BSA) [26]. In this study, only those patients with skin lesions involving 10–15% BSA will be included in the severe group.

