Patients with mild-to-moderate plaque psoriasis will be randomly assigned to one of two groups in a 1:1 ratio, where one group will receive JYG and moving cupping placebo therapy and the other group will receive JYG placebo (JYGP) and moving cupping therapy. The patients in these two groups will be evaluated after 4 weeks of treatment. If a 75% reduction in the PASI (PASI 75) is achieved, treatment will be continued until the end of the 8-week study. Otherwise, patients receiving the moving cupping placebo therapy will be switched to moving cupping therapy, and those receiving JYGP will be switched to JYG for the subsequent 4 weeks of treatment. Patients with severe plaque psoriasis will be randomly assigned to one of three groups in a 1:1:1 ratio to receive JYG, moving cupping therapy and NB-UVB placebo therapy, or JYGP, moving cupping placebo therapy and NB-UVB therapy, or JYG, moving cupping therapy and NB-UVB therapy (Fig. 1). At each visit, we will evaluate and record the relevant patient efficacy indicators and TCM symptom information and obtain images of target lesions. This manuscript has been written in accordance with the Standard Protocol Items: Recommendations for Interventional Trials (SPIRIT) 2013 checklist (see Additional file 1). The results of the study will be disseminated to the public through conference reports and open-access journals.

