### Assignment of interventions: allocation

#### Sequence generation

Eligible patients with mild-to-moderate or severe psoriasis will be enrolled at each of the six participating institutions and will be randomized separately. During their second visit, patients with mild-to-moderate psoriasis will be randomly assigned to either group A or group B in a 1:1 ratio, while those with severe psoriasis will be randomly assigned to group C, group D or group E in a 1:1:1 ratio. Randomization will be performed using a computer-generated random assignment sequence through the central layering and block randomization method of SAS software (V.9.4).

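### The week-4 switch cannot show whether or when to add internal or external TCM; the mild-to-moderate design supports only a comparison of two starting strategies

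*Protocol article*

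**What the plan says.** **The claim.** Under Trial design, the Protocol article says the trial "aims to determine the appropriate time for the intervention with TCM". The Discussion says the mild-to-moderate design allows the internal and external treatments to be compared, "but also enables an assessment of the intervention opportunities for internal and external treatment with TCM". Later in the Discussion, more loosely: "The results will provide a new perspective on the timing and options for therapy". The phrase about intervention opportunities is vague on its own, but the other two statements show that timing is meant.

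**The design.** Under Sequence generation, "patients with mild-to-moderate psoriasis will be randomly assigned to either group A or group B in a 1:1 ratio". Under Trial design, "The patients in these two groups will be evaluated after 4 weeks of treatment". For those who respond, "If a 75% reduction in the PASI (PASI 75) is achieved, treatment will be continued until the end of the 8-week study". For everyone else, over the last 4 weeks: "Otherwise, patients receiving the moving cupping placebo therapy will be switched to moving cupping therapy, and those receiving JYGP will be switched to JYG". Because a placebo is replaced by its active counterpart, the switch is in effect an add-on: from then on the patient receives both JYG and cupping.

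**Change over time.** To justify the 8-week treatment cycle, the Discussion cites a report that "the efficacy of moving cupping therapy in the 8-week treatment of plaque psoriasis was higher than that in the 4-week treatment".

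**The concern.** To learn whether adding a component helps patients who have not responded, some non-responders must receive it and comparable ones must not. To learn when to add it, at least two start times must be compared. The mild-to-moderate stratum offers neither comparison. The only evidence on the addition is how switched patients change between weeks 4 and 8, and those patients were selected for a poor result at week 4. Such a change mixes the added component with:

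- continued effect of the first treatment;
- the emollient that all groups receive, which the Discussion says can itself relieve psoriasis;
- regression to the mean after selection on a low response.

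At stake is a property that the protocol says the design has. The trial is meant to feed treatment norms, so a timing conclusion drawn from it could be carried into practice without a comparison behind it. The limitations in the Discussion do not mention this.

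**Working it through.** The point concerns structure, so the check is to list the contrasts and see what each identifies.

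**1. What the sample size covers.** Inputs from the Sample size section: 30% in A, 59% in B, alpha 0.05 (two-sided per Statistical methods), power 80%. With the unpooled normal formula:

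n = (1.96 + 0.8416)² × (0.30×0.70 + 0.59×0.41) / (0.59 − 0.30)² = 7.849 × 0.4519 / 0.0841 = 42.2, rounded up to 43 per group.

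This reproduces the stated 43. The figure serves one contrast, A v B. The section gives no sample size for a switch or timing comparison.

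**2. What each available comparison identifies.**

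| Comparison | Randomised? | What it identifies |
|---|---|---|
| A v B at week 4 | Yes | Internal v external treatment, before any switch |
| A v B at week 8 | Yes | Two whole strategies: internal first v external first, each with add-on for non-response |
| Switched v unswitched non-responders | Does not exist: 0 unswitched by design | – |
| Switched non-responders v week-4 responders | No; groups are defined by outcome | Neither the add-on effect nor timing |
| Switched patients, week 4 v week 8 | No; before-after in a selected group | Total change from all causes |
| Addition at week 4 v another time | Does not exist: one switch time, no arm on both components from week 0 | – |
| Groups C, D, E | Yes, but in the severe stratum, randomised separately, with no week-4 switch | Fixed regimens from week 0 |

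**3. Can the severe stratum fill the gap?** E v D shows the effect of giving JYG and cupping together on top of NB-UVB from the start. It does not separate JYG from cupping, does not vary the start time, and concerns different patients.

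**4. Is change after week 4 plausible without a switch?** For cupping, yes, on the protocol's own statement that 8 weeks did better than 4. That bears on group B. The document makes no matching statement for JYG, so for group A this is only a possibility.

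**5. Does another section alter the picture?** Intervention description sets out A and B as given for 8 weeks and does not repeat the week-4 change in Trial design. The two should be reconciled. Read either way, there is no comparison of adding with not adding, or of one time with another.

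**The case against.** **Timing is not the main aim.** The Abstract speaks of the sequence of internal and external treatments in this stratum, and Objectives speaks of optimising treatment and setting norms. Timing appears in one clause of Trial design and in looser Discussion wording. This stands: the point is that one stated aim exceeds the design, not that the trial's purpose fails.

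**The design delivers useful randomised evidence.** This also stands. Week-4 and week-8 A v B bear directly on the sequence question. The share in each arm needing adjustment at week 4 can also be estimated, which is one fair reading of the Discussion's remark on the necessity to adjust treatment.

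**The full protocol or SAP may deal with it.** How switched patients are tabulated can be left there. A comparator that the allocation scheme does not contain cannot be supplied by any analysis plan.

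Three stronger readings are tempting, and the documents do not support them.

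- A reader might infer that the trial will report the week 4-8 gain in switched patients as benefit of the switch. No section plans that analysis; Statistical methods describes comparisons among groups, including over several time points.
- A reader might try to size the spurious gain from the 59% planned for B. If that were an unswitched week-8 PASI 75 rate, if x were the week-4 rate, and if no early responder lost response, the share of non-responders responding later without a switch would be (0.59 − x)/(1 − x). This runs from 59% at x = 0 to 0% at x = 59%. The protocol gives no x, no time point for the 59%, and does not say that efficacy there means PASI 75. No trial-specific size follows.
- A reader might take all of the later gain to be time course. The cited report concerns cupping only and, as quoted, says nothing about week-4 non-responders. The most that can be said is that part of the gain may have other causes.

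**Conclusion.** The concern holds as a claim that exceeds the design. The trial cannot identify the effect of adding JYG or cupping after non-response, or the time at which to add it. The size of the gap is structural: zero non-responders randomised to stay unswitched and one switch time, whatever the enrolment. This rests only on the allocation scheme and the week-4 rule as written, and needs no assumed response rate. Week-4 A v B remains a randomised comparison of internal with external treatment, and week-8 A v B remains a valid comparison of two strategies. The trial can therefore inform which treatment to start with, but not whether or when to add the other. The correction should be made because it limits what the trial may conclude; it alters no arm, endpoint, sample size or specified between-group analysis.

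**What to change.** - In Trial design and in both Discussion statements, replace the timing claim with what the design supports: internal v external treatment at week 4, and internal-first v external-first strategies, each with add-on for non-response, at week 8.
- State that week 4-8 results in switched patients are descriptive, shown by arm, with no inference about the effect or timing of the added component.

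The cost is a few sentences of wording. The downside is that the sponsor gives up a timing claim that the design cannot support.

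Keeping the claim would instead require a randomised contrast among non-responders, which the planned numbers would not carry well. As an illustration, assume 50% to 95% of the 108 patients are non-responders at week 4. Splitting them in two within each arm gives 108 × 0.50 / 4 = 13.5 to 108 × 0.95 / 4 = 25.7 per cell, against the 43 per group that the protocol requires for A v B. Recruitment is also reported as under way, so the wording change is the practical course.

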## Trial status

This is protocol version 3.0 (3 May 2019). Patient recruitment began in September 2019 and is expected to be completed by the end of September 2021. The study procedures are expected to be completed by the end of December 2021.

## Data Availability

Not applicable.

## Abbreviations

TCM: Traditional Chinese medicine
WM: Western medicine
JY: Jueyin
PASI: Psoriasis Area and Severity Index
NB-UVB: Narrow-band ultraviolet B radiation
JYG: Jueyin granules
BSA: Body surface area
JYGP: Jueyin granules placebo
PASI 75: 75% reduction in the Psoriasis Area and Severity Index
PGA: Physician’s global assessment
VAS: Visual analog scale
DLQI: Dermatology Life Quality Index
PRQoL: Patient-reported quality of life
AE: Adverse event
SAE: Serious adverse event
trAE: Treatment-related adverse event
IL: Interleukin
